## 9.2 Statistical analyses

### 9.2.1 Sample size calculations

The assessment of the primary endpoints in this trial are based on the RAND 36-item health survey at baseline and 3 months where the domains of physical functioning and role functioning/physical defines the primary endpoints.

The primary endpoints have been used for long COVID (Garratt et al., 2021). There are norm data available for Sweden which enable us to determine a threshold for normalisation of individual RAND 36 domain levels. Using data from a few studies with similar methodology where RAND 36 has been previously used, we have assumed the standard deviation (SD) of Role Physical (RP), Physical Functioning (PF) 15.0. We expect the quality of life to be generally low in our cohort, especially in the RAND 36 RP and PF domains. We consider a ten points higher RAND 36 score in the HBO group compared to the placebo group to constitute a clinically relevant difference to be detected. Sample size calculation using t-test for independent groups, with 80% power, assuming a common SD of 15, and with a 5% significance level, reveals that at least 37 subjects per group are needed. We aim to recruit 80 subjects. An interim analysis will be made after 20 have undergone visit 2 to evaluate safety and when 40 subjects have undergone visit 3 in order to stop for futility and adjustment of sample-size if needed.

Sample size calculation was done in nQuery version 7.

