### 9.2.2.2 Adjustment for Multiplicity

The overall type I error rate for testing the primary efficacy endpoints will be controlled at the type I error rate of 0.05 using appropriate methods for adjustment of multiplicity in the primary. There will be no adjustment for multiplicity in main secondary endpoints but nominal p-values will be presented and results will be interpreted as exploratory findings.

All hypothesis tests will be two-sided. Details of the methods for adjustment in terms of the selection of endpoints to include in the testing sequence and the criteria for rejecting (or not rejecting) individual hypotheses are provided in the SAP.

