#### 9.2.4 Primary Endpoint Analysis

The analysis of the primary endpoint will be conducted on the Full Analys Set (FAS) and the Per Protocol Set (PPS).

The primary analysis of the primary endpoints will be performed using the ANCOVA, including randomisation strata of main symptom and gender together with treatment as fixed factors in the model.

The two primary endpoints will be adequately adjusted for multiplicity. The p-value for testing the null hypotheses, no difference between treatment groups, must be less than 0.05 to be considered to have met the primary objective.

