#### 9.2.7 Interim Analysis

Safety will be monitored continuously by the DSMB throughout the trial, an interim safety analysis will be performed when 20 subjects have available data for the safety endpoints.

There will be an interim analysis performed after 40 subjects have available data for the primary endpoint. The purpose of the interim analysis is to evaluate the assumption used for the sample size calculation and if necessary, to adjust the sample-size if needed. Also, the study will be evaluated for futility regarding the primary endpoints, to stop the study for futility (i.e., the predictive probability of success at the end of the study, given the data at the interim analysis) is less than 20%.

The DSMB will perform both interim analyses. A separate DSMB protocol will be created.

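### The 80% power in section 9.2.1 is for one unadjusted 5% test and reflects neither the two adjusted primary tests nor the futility stop

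*Protocol*

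**What the plan says.** Section 9.2.1 defines the two RAND 36 domains RP and PF as the primary endpoints. The difference to be detected is "a ten points higher RAND 36 score in the HBO group compared to the placebo group". The calculation is for a two-sample t-test. Its power and spread are stated as "with 80% power, assuming a common SD of 15"; the conclusion that the section draws from these inputs is "and with a 5% significance level, reveals that at least 37 subjects per group are needed". The recruitment target is 80, and no dropout rate is given.

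Section 9.2.2.2 says: "The overall type I error rate for testing the primary efficacy endpoints will be controlled at the type I error rate of 0.05". It adds "All hypothesis tests will be two-sided" and leaves the method and the criteria for rejecting each hypothesis to the SAP. Section 9.2.4 says "The two primary endpoints will be adequately adjusted for multiplicity" and then sets a threshold of 0.05 for the p-value, in the singular. The synopsis repeats this.

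Section 9.2.7 places an interim analysis at 40 subjects with primary endpoint data. The trial may be stopped for futility if "the predictive probability of success at the end of the study, given the data at the interim analysis) is less than 20" percent, and the sample size may be adjusted at the same look.

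**The concern.** The sample size justification is given in the protocol as a finished calculation, and it sizes one test "with a 5% significance level". The analysis described in the same chapter is different: two tests share an overall 5%, with a chance of stopping early for futility. The 80% is therefore not shown to be the power of the planned analysis.

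At stake is how a null result is read. If the adjusted test is less powerful than the single test, a reader would credit the trial with more sensitivity than it had. The futility rule has the same gap, because its predictive probability needs a definition of success in the middle of the trial, while section 9.1 requires the SAP to be final only before database lock.

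**Working it through.** **Inputs.** From 9.2.1: difference δ = 10, SD σ = 15, 80% power, alpha 5%, 37 per group, 80 to be recruited (40 per group with the 1:1 allocation of 7.5). From 9.2.2.2: two-sided tests. From 9.2.7: interim at 40 subjects, futility threshold 20%. Assumed, because the protocol does not give them: RP-PF correlation 0 to 0.9, no dropout, 20 per group at the interim, and a flat prior for the predictive probability.

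**1. The stated figure.** Power is the probability that a noncentral t, with 2n − 2 degrees of freedom and noncentrality (δ/σ)√(n/2), exceeds the two-sided critical value.

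- n = 37, alpha 0.05: noncentrality 0.667 × √18.5 = 2.867, critical value 1.993, power 80.8%. With n = 36 it is 79.7%. So 37 is reproduced as a single, two-sided, unadjusted test.
- n = 40, alpha 0.05: noncentrality 0.667 × √20 = 2.981, critical value 1.991, power 83.8%.

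**2. One domain at alpha 0.025 (Bonferroni).**

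- n = 37: critical value 2.289, power 72%.
- n = 40: critical value 2.285, power 76%.
- 45 per group are needed for 80% (power 80.9%; 44 falls just short).
- With 40 per group, the difference detectable with 80% power is 10.5 points.

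**3. Two domains, a 10-point effect in each.** At correlation 0 the results follow by hand; at correlation 0.9 they come from simulating two correlated t-tests.

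- Both required at 0.05, correlation 0: 0.808² = 0.65 and 0.838² = 0.70.
- At least one at 0.025, correlation 0: 1 − (1 − 0.718)² = 0.92 and 1 − (1 − 0.756)² = 0.94.
- Holm per domain, correlation 0: 0.718 + (0.808 − 0.718) × 0.718 = 0.78 and 0.756 + (0.838 − 0.756) × 0.756 = 0.82.

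| Rule | 37 per group | 40 per group |
|---|---|---|
| 0.025 per domain (Bonferroni) | 72% | 76% |
| Both domains required at 0.05 | 65-76% | 70-79% |
| Holm, per domain | 76-78% | 79-82% |
| Hochberg, per domain | 78-79% | 81-82% |
| At least one domain, Bonferroni or Holm | 78-92% | 81-94% |
| First domain of a fixed sequence | 81% | 84% |

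Ranges run over correlations 0 to 0.9. For the both-domains rule the low end is at correlation 0; for the Holm, Hochberg and at-least-one rows it is at 0.9.

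**4. Effect in one domain only.** Bonferroni, Holm and Hochberg all give about 72% with 37 per group and 76% with 40 for the domain that responds.

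**5. Futility stop, one domain, normal approximation.** With information fraction f = 20/n, the predictive probability is Φ[(z₁/√f − z_α)/√((1 − f)/f)], where z_α is the two-sided critical value. It is below 20% when z₁ < √f × z_α − 0.842 × √(1 − f). With 40 per group, f = 0.5 and z₁ has mean 2.981 × 0.707 = 2.108.

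- Alpha 0.05: stop if z₁ < 0.707 × (1.960 − 0.842) = 0.79. Stopping probability Φ(0.79 − 2.108) = 9.4%. Power falls from 84.6% to 81.1%.
- Alpha 0.025: stop if z₁ < 0.707 × (2.241 − 0.842) = 0.99. Stopping probability Φ(0.99 − 2.108) = 13.2%. Power falls from 77.0% to 73.1%.

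The starting values are about one point above the t-based figures because of the approximation; the loss, about 3.5 to 4 points, is what matters.

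**The case against.** The strongest reply is that no shortfall has been shown. A reader might infer that the trial does not deliver 80% power, or that it needs 90 subjects. The documents do not support that. The rejection rule is left to the SAP, which is not at hand, and that is a legitimate place for it. At the planned 40 per group, several ordinary rules reach 80% before futility when both domains respond: at least one domain, Hochberg per domain, the first domain of a fixed sequence and, roughly, Holm per domain. The figure of 45 per group applies only to a Bonferroni split with 80% wanted in each domain.

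The futility loss is also an upper figure for its model. Section 10.6 leaves stopping to the sponsor on the DSMB's advice, and a separate DSMB protocol may define the calculation. For a single 5% test with 40 per group, about 81% remains after the stop. The same interim may change the sample size. ANCOVA may gain precision over the t-test: if SD 15 is unadjusted, a covariate-outcome correlation of about 0.33 would bring a 0.025 test with 40 per group to about 80.7%. The protocol states no such correlation.

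A reader might also take the 0.05 threshold in 9.2.4 as an unadjusted test of each domain, which would inflate the type I error. It directly follows the commitment to adjust, and 9.2.2.2 holds the overall rate at 0.05, so an adjusted p-value is the natural reading. The wording is loose, not evidence of inflation.

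All of this stands, and it makes the shortfall conditional. It does not make the printed 80% the power of the planned analysis: that holds only under some of the rules still open, and the calculation names none of them.

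**Conclusion.** The point holds in conditional form. The arithmetic behind 37 per group is right, but it answers for one unadjusted test, while the protocol plans two adjusted tests and a futility stop. At 40 per group the power before futility can lie anywhere from 70% to 94%, depending on the adjustment method, on whether one or both domains must succeed, and on the RP-PF correlation. It is clearly below 80% for a Bonferroni split per domain, and for Bonferroni, Holm or Hochberg when only one domain responds; it stays below 80% throughout if both domains are required. These figures rest on the protocol's own difference and SD and on the assumptions listed in the working. Type I error and the treatment estimate are not affected. This should be fixed, but it does not threaten the trial's validity.

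**What to change.** - In 9.2.1, replace the single-test 80% with the power, or the detectable difference, at the planned 40 per group for the adjusted test and success rule actually used, with the futility stop included. Under a 0.025 split, for example, this would be 76% per domain before futility (about 73% with the rule followed automatically) and a detectable difference of 10.5 points at 80% power. Under another rule, use that rule's figures.
- In 9.2.7, use the same definition of success in the predictive probability, and fix it before the interim look.
- In 9.2.4 and the synopsis, say that the multiplicity-adjusted p-value must be less than 0.05.

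The cost is protocol and SAP wording. No extra patients are needed. The only downside is a slightly less favourable stated power under some rules.

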### 9.2.2 General statistical methodology

Primary and secondary endpoints will be evaluated using the FAS population and sensitivity analyses performed using the PP population.

Trial Code: HOT-LOCO  
Version No: v.4  
Date: 2022-01-03  
EudraCT No: 2021-000764-30

### 9.2.2.1 Statistical Hypotesis

The primary objective of the study is to confirm a superior efficacy for the active treatment compared to placebo in the primary endpoints. The null hypothesis to be tested is that there is no difference between HBO treatment and placebo, i.e., the mean change in (HBOT) = mean change (placebo). The same statistical hypothesis will be used for key secondary endpoints.

### 9.2.2.2 Adjustment for Multiplicity

The overall type I error rate for testing the primary efficacy endpoints will be controlled at the type I error rate of 0.05 using appropriate methods for adjustment of multiplicity in the primary. There will be no adjustment for multiplicity in main secondary endpoints but nominal p-values will be presented and results will be interpreted as exploratory findings.

All hypothesis tests will be two-sided. Details of the methods for adjustment in terms of the selection of endpoints to include in the testing sequence and the criteria for rejecting (or not rejecting) individual hypotheses are provided in the SAP.

### 9.2.2.3 Subgroups

The following subgroups will be evaluated for this study:

- Gender
- Disease severity
  - RAND-36 RP and PF below 30
  - RAND-36 RP and PF 30-50
  - RAND-36 RP and PF above 50

## 9.2.3 Patient Demographic and Baseline Characteristics

Baseline values and patient characteristics will be presented in tables by group and in total. All continuous variables will be described using standard statistical measures, i.e., number of observations, mean and median value, standard deviation, minimum and maximum value. All categorical variables will be summarised in frequency tables.

In general, continuous outcome variables will be analysed using ANCOVA, unless otherwise specified. Estimates will be presented using least square means for differences between treatment arms. For continuous endpoints that are measured repeatedly over time, such as EQ5D, RAND-36 domains, the change from baseline will be analyzed using a linear mixed effect model including baseline, treatment group, sex, symptom severity, visit, and treatment

|             |                |
|-------------|----------------|
| Trial Code: | HOT-LOCO       |
| Version No: | v.4            |
| Date:       | 2022-01-03     |
| EudraCT No: | 2021-000764-30 |

group by visit interaction, and subjects as random effects, in the models. An unstructured covariance matrix will be assumed.

Analysis for categorical data in terms of binary data (Yes/No) will be presented as the proportion of participants with the frequency of presence or absence by treatment group of the characteristics of interest and analysed using the CMH Chi-square test, where the parameter used for the statistical hypothesis testing will be the OR, as a measure of the relative difference in odds between treatment arms. An  $OR > 1$  indicates an efficacy in favour of HBOT compared to placebo.

#### 9.2.4 Primary Endpoint Analysis

The analysis of the primary endpoint will be conducted on the Full Analys Set (FAS) and the Per Protocol Set (PPS).

The primary analysis of the primary endpoints will be performed using the ANCOVA, including randomisation strata of main symptom and gender together with treatment as fixed factors in the model.

The two primary endpoints will be adequately adjusted for multiplicity. The p-value for testing the null hypotheses, no difference between treatment groups, must be less than 0.05 to be considered to have met the primary objective.

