| Trial period:        | Q3 2021 – Q4 2023                                                                                                                                                                                                                                                                                                                                                                                                                                                                                                                                                                                                                                                                                                                                                                                                                                                                                                                                                                                                                                                                                                  |
| Statistical analyses | 
The analysis of the primary endpoint will be conducted on the Full Analys Set (FAS) and the Per Protocol Set (PPS).
 
The primary analysis of the primary endpoints will be performed using the ANCOVA, including randomisation strata of gender and disease severity together with treatment as fixed factors in the model.
 
The two primary endpoints will be adequately adjusted for multiplicity. The p-value for testing the null hypotheses, no difference between treatment groups, must be less than 0.05 to be considered to have met the primary objective.
                                                                                                                                                                                                                                                                                                                                                                                                                                                                                                                            |

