## 7.5 Randomization

Subjects will be enrolled consecutively, as they are found to be eligible for inclusion in the trial, and randomized but after the treatment has been scheduled. Treatment should start within two weeks of randomization.

If a subject discontinues their trial participation, their subject code will not be reused, and the subject will not be allowed to re-enter the trial again. There will be no replacement for these subjects.

Eligible subjects will be randomized in a 1:1 allocation, stratified by disease severity in relation to RAND 36 and gender in blocks (blinded to all study personnel) to either HBO2 or Placebo. There will be a computer generated randomization.

|             |                |
|-------------|----------------|
| Trial Code: | HOT-LOCO       |
| Version No: | v.4            |
| Date:       | 2022-01-03     |
| EudraCT No: | 2021-000764-30 |

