#### 9.2.5 Secondary Endpoints Analysis

The same analysis approach used for the primary efficacy endpoint will be applied to the secondary efficacy and exploratory endpoints as for the primary endpoints referred to as a 'Proportion endpoints'.

For categorical secondary endpoints, the CMH Chi-square test adjusting for disease severity and gender will be used to test for differences between treatments. Results will be presented using the frequency and the proportion by treatment group and the OR together with its corresponding 95% confidence interval.

All tests for the secondary endpoints will be two-sided on the 0.05 significance level. There will be no adjustment for multiplicity in main secondary endpoints.

All analysis will be done for the FAS population using observed data.

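### Section 9.2.4 puts 'main symptom' where randomisation, the synopsis and section 9.2.5 have disease severity, so the protocol contradicts itself on the primary ANCOVA

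*Protocol*

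**What the plan says.** The protocol describes the adjustment factors in five places.

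- **Section 7.5 (Randomization):** allocation is 1:1, "stratified by disease severity in relation to RAND 36 and gender in blocks".
- **Section 9.2.4 (Primary Endpoint Analysis):** the primary ANCOVA is run "including randomisation strata of main symptom and gender together with treatment as fixed factors in the model".
- **Synopsis (Statistical analyses):** the same primary ANCOVA is run "including randomisation strata of gender and disease severity together with treatment as fixed factors in the model".
- **Section 9.2.5 (Secondary Endpoints Analysis):** for categorical endpoints, "the CMH Chi-square test adjusting for disease severity and gender will be used to test for differences between treatments".
- **Section 9.2.3:** repeated continuous endpoints, among them the RAND-36 domains, go into a "linear mixed effect model including baseline, treatment group, sex, symptom severity, visit, and treatment" group by visit interaction.

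Severity bands appear only among the subgroups in section 9.2.2.3, where the lowest is "RAND-36 RP and PF below 30". Apart from 9.2.4, main symptoms are mentioned only in section 5.2.1, to say that the choice of questionnaires and physical tests may vary with them.

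**The concern.** Section 9.2.4 is the operative text for the primary analysis, and it refers to strata that the randomisation does not have. An analyst who follows it must invent a classification of main symptom from a syndrome with many overlapping symptoms, and must leave out severity, on which subjects were randomised. Because 9.2.5 carries the primary approach over to the secondary and exploratory endpoints, the wrong factor could reach the continuous secondary endpoints while the categorical ones adjust for severity.

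Two things are at stake. Stratifying on a prognostic factor and then ignoring it in the model makes the reported standard error too large, which gives away precision in a trial of 80. And two conflicting statements of the primary model leave a covariate choice open that should be closed in advance.

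**Working it through.** **1. The texts side by side**

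| Place | Severity-type factor | Gender/sex |
|---|---|---|
| 7.5, randomisation | disease severity (RAND 36) | yes |
| Synopsis, primary ANCOVA | disease severity | yes |
| 9.2.5, CMH test | disease severity | yes |
| 9.2.3, mixed model | symptom severity | yes |
| 9.2.4, primary ANCOVA | none; main symptom instead | yes |

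Section 9.2.4 is the only one without a severity factor. Since it describes its factors as randomisation strata, it contradicts 7.5 directly and not merely in terminology.

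**2. The plan's own figure**

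Section 9.2.1 states: "Sample size calculation using t-test for independent groups, with 80% power, assuming a common SD of 15, and with a 5% significance level". With a difference of 10 points and two-sided testing, the normal approximation gives 36 per group. The noncentral t distribution gives power of 79.7% at 36 and 80.8% at 37, so the stated 37 per group is reproduced. At 40 per group (80 in total) power is 83.8%. This calculation uses an unadjusted t-test, so the choice of covariates does not alter it.

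**3. Omitting severity, with no baseline score in the model**

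Let severity explain a share R² of the outcome variance. The protocol gives no value; 0.1 to 0.3 is assumed. With arms balanced on severity:

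- true SE of the difference ≈ σ√(2/n) × √(1 − R²)
- SE reported by a model without severity ≈ σ√(2/n)
- ratio of reported to true SE = 1/√(1 − R²)
- approximate type I error = 2[1 − Φ(1.96 × ratio)]

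With σ = 15 and n = 40, σ√(2/n) = 15 × √0.05 = 3.354.

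| R² | true SE | ratio | approx. type I error |
|---|---|---|---|
| 0.1 | 3.182 | 1.05 | 3.9% |
| 0.2 | 3.000 | 1.12 | 2.8% |
| 0.3 | 2.806 | 1.20 | 1.9% |

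A simulation agrees (6,000 runs per setting, 40 per arm, three severity levels balanced between arms, main symptom a three-level factor unrelated to outcome, difference of 10 for power):

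| R² | Type I: main symptom + gender | Type I: severity + gender | Power: main symptom + gender | Power: severity + gender |
|---|---|---|---|---|
| 0 | 4.9% | 5.1% | 83% | 84% |
| 0.1 | 4.0% | 5.2% | 84% | 87% |
| 0.2 | 3.1% | 5.5% | 85% | 91% |
| 0.3 | 2.3% | 5.4% | 86% | 94% |

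The severity model is nominal within simulation error. The main-symptom model is conservative and loses about 3 to 8 points of power for R² of 0.1 to 0.3.

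**4. The same comparison with a baseline score in the model**

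Here severity is a coarse grouping of the baseline score, baseline explains 10% to 30% of outcome variance, and 80 subjects are randomised in blocks of 4 within severity by gender (4,000 runs per setting). Without a baseline covariate, the main-symptom model again gives type I error below 5% (about 4.4% falling to 2.4%). With the baseline covariate, it gives about 5.1% to 5.2%. Power is then 86%, 90% and 94%, against 87%, 90% and 94% for the severity model, and the reported standard errors differ by less than 1%.

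**The case against.** The best defence is that the intended model can be recovered. Section 9.2.4 speaks of randomisation strata, 7.5 says what they are, and the synopsis has an almost identical sentence with disease severity. A reader might infer from 9.2.4 alone that the sponsor has settled on a wrong primary model; the documents do not support that, because another statement of the same model is right. This stands, and it makes the point a self-contradiction that must be resolved.

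The second defence concerns size. Section 9.2.4 names an ANCOVA and lists only its fixed factors, so a baseline covariate is neither stated nor ruled out, and 9.2.3 does include baseline in its mixed model. If baseline is in the primary model, step 4 shows that almost nothing is lost. This also stands, and the loss has to be stated conditionally. It is likewise tempting to call severity the strongest prognostic factor available, since it is built on the outcome scale. The protocol gives no data on prognostic strength, and the continuous baseline score carries at least as much information as bands of it.

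Third, section 9.1 requires the SAP to be final before database lock, which limits any choice of model after the data are seen. That is partly an answer. The SAP is not at hand, however, and this is not a detail left to it: the protocol names the covariates and does so inconsistently.

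**Conclusion.** The contradiction is certain on the text. Section 9.2.4 names a stratum that does not exist and omits one that does, against 7.5, the synopsis and 9.2.5, with a third term in 9.2.3.

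The consequence is modest. The treatment estimate is unbiased under either model. Without a baseline score, and with severity explaining an assumed 10% to 30% of outcome variance, the standard error is overstated by about 5% to 20% and the test is conservative with some lost power. With a baseline score in the model the effect is near zero.

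A reader might infer that the primary test risks false positives or that the trial is undersized. Neither follows: type I error falls or stays nominal, the 37 per group are reproduced and do not depend on the covariates, and even with severity omitted the simulated power is 83% to 86%, above the planned 80%. This is something that should be fixed, not a threat to validity.

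**What to change.** In section 9.2.4, replace main symptom and gender with disease severity and gender, so that it agrees with section 7.5 and the synopsis. State that severity enters the model in the same categories as were used for randomisation. The bands in 9.2.2.3 cannot simply be assumed to be those categories: they are given for subgroups, and they do not say where a subject with, for example, RP 0 and PF 60 belongs. In section 9.2.3, replace symptom severity with the same term.

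The cost is a few words in two sections. The sample size, data collection and randomisation do not change. The correction should be made before unblinding.
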